### 2.5. Statistical Analysis

Basic statistics (absolute and relative frequencies for categorical variables; quartiles, maximum, minimum, and mean for continuous variables; and quartiles and relative frequencies for discrete variables) will be obtained to summarize the distribution of variables related to patient background factors, complications, other prognostic factors, and endpoints.

Kaplan–Meier curves will be obtained for each stratum consisting of patient background and prognostic factors for the occurrence of events associated with various endpoints (overall survival, time to treatment failure, recurrence-free survival, and adverse events). Several univariate logistic regression analyses will be performed, with the presence or absence of events in each stratum as the objective variable and the categorical value of each background or prognostic factor as the explanatory variable.

A hierarchical set of predictive models will be constructed by combining explanatory variables that are expected to contribute a single-layer or multi-layer proportional hazards model, which will be set up by incorporating each predictive model, and Cox multiple regression analysis will be performed. If proportional hazards are not acceptable, parametric hazard models such as the Cure–Weibull gamma-frailty model or the mixed Weibull gamma-frailty model will be applied for survival time analysis (including in combination with logistic regression models) [24]. Based on the likelihood (or partial likelihood in the case of Cox regression), the Akaike information criterion (AIC) and Bayesian information criterion (BIC) will be used to explore the optimal model (if the number of cases covered differs between models, the average AIC and BIC per case are used instead).

Regarding the estimated value of the regression coefficient of the explanatory variable included in the optimal model, if *p* value is <0.05, it will be judged as an important prognostic factor, and the 95% confidence interval of the hazard ratio regarding the magnitude of the contribution of that factor will be calculated.

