## Abstract

Cohort studies using large-scale databases have become increasingly important in recent years. The Tokushukai Medical Group is a leading medical group in Japan that includes 71 general hospitals nationwide from Hokkaido to Okinawa, with a total of 18,000 beds, and a unified electronic medical record system. This retrospective cohort study aims to evaluate the real-world outcomes of systemic therapy for Japanese patients with cancer using this merit of scale. All adult patients with cancer who received systemic therapy using a centrally registered chemotherapy protocol system at 46 hospitals from April 2010 to March 2020 will be identified (~48,850 patients). Key exclusion criteria include active double cancer and inadequate data extraction. Data will be obtained through electronic medical records, diagnosis procedure combination data, medical prescription data, and the national cancer registration system that includes sociodemographic variables, diagnostic and laboratory tests, concomitant drug prescriptions, cost, and overall survival. Kaplan–Meier estimates will be calculated for time-to-event analyses. Stratified/conventional Cox proportional hazards regression analyses will be conducted to examine the relationships between overall survival and related factors. Our findings provide important insights for future research directions, policy initiatives, medical guidelines, and clinical decision-making.

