### 2.3. Study Endpoints

For this study, the primary endpoint is overall survival, whereas the secondary endpoints are the time to treatment failure, recurrence-free survival, and adverse events, evaluated based on the Common Terminology Criteria for Adverse Events v.5.0 Japanese translation—Japan Clinical Oncology Group (JCOG) version (CTCAE v. 5.0-JCOG) [23].

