### Strengths and Weaknesses

This nationwide cohort study will include a large number of patients from community-based general hospitals only, not including cancer centers or academic institutions. The cohort will comprise a certain number of patients who are unable to participate in clinical trials owing to their age, poor performance status, or complications. Therefore, this study could provide more realistic clinical data with a lower rate of loss to follow-up.

Moreover, our study will simultaneously use demographic data and treatment details, as well as the National Cancer Registry, DPC, prescription, and laboratory test data. In particular, few large-scale databases include performance status and laboratory data, which would be major considerations regarding prognostic factors. In addition, by using the DPC data, detailed information on emergency hospitalization, length of hospital stay, concomitant complications, medical costs, and outcomes can be obtained, allowing for a review of the quality and cost-effectiveness of medical care. Prescription data would be useful for evaluating drug–drug interactions. Relative dose intensity can also be computed. Individual analyses using institutional or national databases are very common; however, to the best of the authors’ knowledge, this is the first large-scale cohort study that can simultaneously handle comprehensive RWD.

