In this study, it will be difficult to extract data without using a unified description format or sentences as descriptions in ordinary medical records. For instance, the time to treatment failure is easy to obtain, although there is no distinction between refractory and intolerant. Progression-free survival and recurrence-free survival can only be obtained through direct checks of medical records, although they are less reliable in retrospective studies [25]. In the same context, direct access to medical records is mostly required to obtain information on genetic mutations [26], which becomes an essential step when conducting standard treatment for many cancer types because the Japanese National Cancer Registry does not contain it, and most results of genetic alteration tests are included as images after outsourcing to testing companies. With regard to adverse events, laboratory data can be easily extracted and evaluated; however, it is difficult to handle imaging findings, such as intestinal lung disease, or subjective symptoms, such as nausea and vomiting. The electronic medical record system is equipped with software that evaluates and inputs according to CTCAE, but it is not sufficiently widespread during the current study period. Similarly, there is no provision for the patients’ quality of life scores to be routinely entered in the electronic medical record; thus, it is impossible to extract such data from our medical records, although its usefulness has been established [27]. These limitations indicate if there is good or poor compatibility among sub-projects for each type of cancer and treatment.

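### Section 2.5 plans Kaplan-Meier curves for adverse events and names no competing-risk estimator, so 1-KM read as the proportion affected would overstate incidence, slightly for early events and more for later ones

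*Protocol article*

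**What the plan says.** Section 2.3 makes overall survival primary and adds that "the secondary endpoints are the time to treatment failure, recurrence-free survival, and adverse events", with adverse events graded by CTCAE. Adverse events stand there as an endpoint of their own, not as a composite such as adverse-event-free survival.

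Section 2.5 states that "Kaplan–Meier curves will be obtained for each stratum consisting of patient background and prognostic factors" and applies this "for the occurrence of events associated with various endpoints (overall survival, time to treatment failure, recurrence-free survival, and adverse events". One estimator thus serves four endpoints. The Abstract says the same in general terms: "Kaplan–Meier estimates will be calculated for time-to-event analyses".

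The regression part of Section 2.5 plans Cox models and, where proportional hazards fail, that "parametric hazard models such as the Cure–Weibull gamma-frailty model or the mixed Weibull gamma-frailty model will be applied for survival time analysis". None of these is described as a competing-risk model. The article mentions neither a cumulative incidence function nor a rule for a patient who dies before having an adverse event.

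**The concern.** Death is the event in overall survival, and by convention it counts as an event in time to treatment failure and recurrence-free survival. Kaplan-Meier suits those three. An adverse event is different: a patient who dies first can no longer have it. Kaplan-Meier knows only event or censored, so without a composite definition the death is treated like a loss to follow-up, and the curve describes the risk if nobody died. Its complement is never below the proportion of patients who actually have the event.

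This matters here because the cohort is said to include "patients who are unable to participate in clinical trials owing to their age, poor performance status, or complications", and the curves are to be drawn by background and prognostic factors. Such strata can be expected to differ in mortality. Two strata with the same adverse-event hazard would show the same 1-KM curve even though different proportions of their patients are affected. The bias does not shrink with sample size, so a large cohort gives no protection.

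**Working it through.** The article gives no adverse-event rate, death rate or length of follow-up, so it has no figure of its own to reproduce. The size below is a calculation under stated assumptions.

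**Inputs (all assumed).** Constant cause-specific hazards: *a* for the adverse event, *d* = ln 2 / median overall survival for death. Median survival ranges from 6 to 60 months, since one plan covers 15 cancer types (Table 3). The hazard *a* is set so that 1-KM equals 30% at the end of the accrual window *t*: *a* = −ln(0.7)/*t*.

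**Formulas.**
- Kaplan-Meier complement with deaths censored: 1 − exp(−*a t*) = 30% by construction.
- Cumulative incidence (the quantity Aalen-Johansen estimates): *a*/(*a*+*d*) × [1 − exp(−(*a*+*d*)*t*)].

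**Worked example, steady accrual over 12 months, median survival 6 months.** *a* = 0.3567/12 = 0.0297 per month; *d* = 0.6931/6 = 0.1155 per month. Cumulative incidence = 0.0297/0.1452 × [1 − exp(−0.1452 × 12)] = 0.2046 × 0.825 = 16.9%. The overstatement is 30.0 − 16.9 = 13.1 points.

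**Results for a 1-KM value of 30%.**

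| Window in which the 30% accrues | Median survival | Cumulative incidence | Overstatement (points) |
|---|---|---|---|
| 1 month | 6 months | 28.4% | 1.6 |
| 1 month | 60 months | 29.8% | 0.2 |
| 3 months | 6 months | 25.6% | 4.4 |
| 3 months | 60 months | 29.5% | 0.5 |
| 12 months | 6 months | 16.9% | 13.1 |
| 12 months | 12 months | 22.1% | 7.9 |
| 12 months | 24 months | 25.6% | 4.4 |
| 12 months | 60 months | 28.1% | 1.9 |

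If the 12-month hazard continues to 24 months, 1-KM is 51.0% against a cumulative incidence of 19.8% (median survival 6 months) or 45.3% (60 months).

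**Simulation check.** With 200,000 simulated patients and administrative censoring uniform between 12 and 60 months, the 12-month values were 30.0% against 16.9% (median survival 6 months) and 29.9% against 28.0% (60 months), in line with the formulas.

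**The alternative reading.** If death were counted as an event, the same simulation gives 82.6% at 12 months for median survival 6 months and 39.0% for 60 months. That is the risk of adverse event or death, and mostly reflects death where survival is short.

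**Between strata.** In the 12-month scenario, strata with median survival of 6 and 60 months both show 30% on the 1-KM scale, while the proportions affected differ by 28.1 − 16.9 = 11.2 points.

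**The case against.** The strongest reply is that the article never says deaths will be censored. It gives no event or censoring rule for any endpoint, and such rules are often left to a fuller document. That is right as far as it goes: censoring at death follows from the choice of estimator and is not written. But the estimator itself is fixed in the article, and neither way of handling death within it yields the incidence of adverse events.

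A second reply is that timing governs the size. The article notes that "With regard to adverse events, laboratory data can be easily extracted and evaluated" but does not say when these events occur. If they fall mainly in the first weeks, the bias is a point or two at most in the scenarios above. This stands, and it is why early windows belong in the range.

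Third, a reader might infer that the error is always worst in the cancers with the poorest survival. That needs similar adverse-event hazards and timing across cancers treated with different regimens, which the article does not establish.

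Fourth, a reader might infer that all comparisons between strata are spoiled. They are not. A Cox model for adverse events with deaths censored is a cause-specific model, and its hazard ratios are valid as such. What fails is the comparison of absolute incidence read from the curves.

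Finally, Section 2.5 also plans descriptive frequencies for the endpoints and logistic regressions on event presence. These are not Kaplan-Meier estimates and fall outside this point, but they do not correct the curves either.

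**Conclusion.** The point holds as a defect in the estimator named for one secondary endpoint, and should be fixed. Read as the proportion affected, 1-KM with deaths censored overstates adverse-event incidence. The direction is a mathematical result; the size is not known from the article. Under constant hazards and a 1-KM value of 30%, it runs from negligible (0.2 points, events within 1 month, median survival 60 months) to substantial (13.1 points, steady accrual over 12 months, median survival 6 months), and it grows with the time horizon. At similar adverse-event hazards and timing it is larger where mortality is higher, so absolute incidence is not comparable between such strata.

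It would go too far to say that the plan states censoring at death, that a large bias is certain, or that the main results are compromised. Overall survival, the primary endpoint, is unaffected; time to treatment failure and recurrence-free survival are unaffected provided death counts as an event in them.

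**What to change.** In Section 2.5, take adverse events out of the Kaplan-Meier list and state that their incidence will be estimated by the Aalen-Johansen cumulative incidence function, with death without the event as a competing event. Keep Kaplan-Meier for overall survival, and for time to treatment failure and recurrence-free survival with death stated to count as an event. Label any Cox model for adverse events as cause-specific; this clarifies what its hazard ratios mean and changes no computation.

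The cost is a sentence or two. Dates of death and of last survival confirmation are already collected (Section 2.2), and the estimator is standard in R and SAS, both of which Section 2.2 names for the analysis.

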### 2.2. Information Source and Data Collection

Information on the patients who met the inclusion criteria will be extracted by the Tokushukai Information System Inc., while researchers will be blinded to statistical analyses. Figure 1 provides an overview of how variables will be collected.

Patient demographic data, including age, birth year and month, sex, postal code, and insurance type, were documented at the time of the issuance of medical record identification. In addition, body height, body weight, body mass index, body surface area, and date of measurement were recorded based on practical requirements. Moreover, the date of the last visit, the last date of survival confirmation, the date of death, and the diagnosis on medical receipt were automatically recorded as part of routine clinical practice. The above information can be extracted from a unified medical record system (e-Karte and Newtons2, Software Service, Inc., Osaka, Japan).

Treatment information, including inpatient and outpatient therapies, particularly chemotherapy regimens, can be retrieved from a shared chemotherapy protocol system (SSI srvApmDrop, Software Service, Inc., Tokyo, Japan). This system links the start and end date, the date of administration, the treatment interval, the number of treatment cycles, the dose of administration, the data of dose adjustment, and the performance status.

Data from the Japanese National Cancer Registry [19,20] are available for all hospitals, including the diagnosis (date, site, laterality, pathology, and differentiation), staging (clinical and pathological TNM classification [21]), date of the first visit, treatment details (surgery, endoscopic treatment, radiotherapy, chemotherapy, and endocrine therapy), and survival outcomes (last date of survival confirmation, date of death, and cause of death).

Patient, treatment, and cancer registry data are combined with anonymized identification and cleaned by Tokushukai Information System Inc. (Osaka, Japan). Patients with double cancer and/or diagnostic errors will be excluded from the study. Treatment history will be organized, and missing data will be supplemented by a direct check of medical records in cases of inconsistency or lack of information. Patients with unknown treatment history will be also excluded.

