## Figures and Tables

**Figure 1 healthcare-10-02146-f001:**
[figure not shown]
Data collection overview.

**Table 1 healthcare-10-02146-t001:** Inclusion and exclusion criteria.

Inclusion Criteria
Patients with pathologically or radiologically diagnosed cancer Age ≥20 years Receiving centrally registered systemic therapy at DPC hospitals within the Tokushukai Medical Group from 1 April 2010 to 31 March 2020
Exclusion criteria
Patients who chose to opt out Simultaneous and metachronous double cancer with disease-free interval of ≤5 years, except for carcinoma in situ/intramucosal cancer cured by local treatment or endoscopic lesions diagnosed as carcinoma in situ Inadequate data extraction (e.g., missing details on past cancer treatment at other hospitals or individual patient data)

**Table 2 healthcare-10-02146-t002:** Laboratory test information.

Blood cell counts	White blood cell (WBC), red blood cell (RBC), hemoglobin (Hb), platelet (PLT), leukocyte fraction, lymphocyte (Lym), neutrophil (Neu), monocyte (Mono), eosinophil (Eo), and basophil (Baso)
Biochemical tests	Sodium (Na), potassium (K), chloride (Cl), calcium (Ca), inorganic phosphorus (IP), magnesium (Mg), aspartate aminotransferase (AST), alanine aminotransferase (ALT), lactate dehydrogenase (LDH), alkaline phosphatase (ALP), γ-glutamyl transpeptidase (GGT), total bilirubin (T-Bil), direct bilirubin (D-Bil), blood urea nitrogen (BUN), creatinine (CRE), uric acid (UA), total protein (TP), albumin (Alb), blood glucose (Glu), hemoglobin A1c (HbA1c), total cholesterol (TC), HDL cholesterol, triglyceride (TG), C-reactive protein (CRP), iron (Fe), and ferritin
Tumor markers	Squamous cell carcinoma-related antigen (SCC), cytokeratin 19 fragment (SYFRA), carcinoembryonic antigen (CEA), carbohydrate antigen 19-9 (CA19-9), carbohydrate antigen 15-3 (CA15-3), carbohydrate antigen 125 (CA125), neuron-specific enolase (NSE), pro-gastrin-releasing peptide (ProGRP), and prostate specific antigen (PSA)
Coagulation/fibrinogenic tests	Activated partial thromboplastin time (APTT), prothrombin time (PT), fibrinogen (Fib), fibrin/fibrinogen degradation product (FDP), and D-dimer
Infectious disease markers	Hepatitis B surface (HBs) antigen, HBs antibody, HB core antibody, HBe antigen, HBe antibody, HB virus DNA quantification, HC virus antibody, syphilis, and HIV
Urinalysis parameters	Urine protein qualitative, urine sugar qualitative

**Table 3 healthcare-10-02146-t003:** Sample size of each cancer type.

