Biliary tract cancer	800
Breast cancer	10,000
Colorectal cancer	10,000
Esophageal cancer	1000
Gastric cancer	5000
Gastrointestinal stromal tumor	500
Kidney cancer	350
Liver cancer	500
Lung cancer	10,000
Ovarian cancer	1500
Prostate cancer	5000
Pancreatic cancer	2500
Uterine body cancer	350
Uterine cervix cancer	350
Urothelial cancer	1000

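### The univariate logistic regressions are fixed to categorised factors although many candidate factors are continuous, which loses information and makes the univariate results depend on unstated cut-points

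*Protocol article*

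**What the plan says.** All of the relevant analysis text is in section 2.5 of the protocol article.

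- Description: continuous variables are recognised as such and summarised by "quartiles, maximum, minimum, and mean for continuous variables".
- Display: "Kaplan–Meier curves will be obtained for each stratum consisting of patient background and prognostic factors", which requires groups.
- Univariate regression: the article takes "the categorical value of each background or prognostic factor as the explanatory variable". The same sentence names the model and the outcome to which this coding applies: "Several univariate logistic regression analyses will be performed, with the presence or absence of events in each stratum as the objective variable".
- Multivariable modelling comes in the next paragraph: "A hierarchical set of predictive models will be constructed by combining explanatory variables". Nothing is said here about how a continuous variable enters. The p<0.05 rule for calling a factor important applies to coefficients in the model selected at this stage.

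The candidate factors are described elsewhere. Section 2.2 records age and states that "body height, body weight, body mass index, body surface area, and date of measurement were recorded based on practical requirements". Table 2 starts with "White blood cell (WBC), red blood cell (RBC), hemoglobin (Hb), platelet (PLT" and goes on through biochemistry, tumour markers and coagulation tests. Table 3 gives the expected cohort sizes, from 350 (for example "Uterine cervix cancer") to 10,000.

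**The concern.** The instruction to categorise applies to each factor, with no exception for measurements on a continuous scale. The same section separates variable types for description and then drops the distinction for regression. This is a stated coding choice, so it cannot be put down to detail left to a fuller document.

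Grouping a continuous factor treats all patients within a group as alike and puts a step at each boundary. Two things follow for the univariate step:

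- Part of the factor's information is discarded, so a real association is more easily missed.
- The estimate and p-value change with the cut-points, and none are given. With dozens of laboratory values and 15 cancer types, this leaves a lot of room for results that reflect the threshold and not the factor.

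The article presents laboratory data as one of the cohort's distinguishing strengths for prognostic work (Discussion, Strengths and Weaknesses), so the coding weakens the data on which the study relies most.

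**Working it through.** **The plan's own figure.** The article states no power, effect size or information loss. Its one checkable figure is the total of about 48,850 patients. The 15 rows of Table 3 sum to 48,850, so it reproduces.

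**How many factors are continuous.** Table 2 lists 61 entries. About 50 are numeric: 10 blood counts + 26 biochemical tests + 9 tumour markers + 5 coagulation tests. Age, height, weight, body mass index and body surface area add to these. Sex, stage, pathology, performance status, most infection markers and qualitative urinalysis are categorical or ordinal.

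**Information kept after grouping.** Assume a standard normal factor with a linear effect. For categories with probability p and lower and upper limits a and b, the fraction kept for a small effect is Σ (φ(a) − φ(b))² / p. For a median split this is 2/π = 0.637.

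| Coding (assumed) | Kept | Lost |
|---|---|---|
| Median split | 0.637 | 36.3% |
| 70/30 | 0.576 | 42.4% |
| 80/20 | 0.490 | 51.0% |
| 90/10 | 0.342 | 65.8% |
| Tertiles | 0.793 | 20.7% |
| Quartiles | 0.861 | 13.9% |
| Quintiles | 0.897 | 10.3% |

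A logistic simulation (n = 2,000, odds ratio 1.3 per SD, 400 replicates, likelihood-ratio statistic minus its degrees of freedom, relative to the continuous fit) agrees: 0.633 for the median split, 0.488 for 80/20, 0.797 for tertiles and 0.864 for quartiles.

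**What this does to power.** The article gives no event counts or effect sizes, so those below are assumptions. Power for one degree of freedom = Φ(√(deaths × kept) × ln HR − 1.96). This is a hazard-ratio formula, used to show scale; the fractions kept are the ones checked above under logistic regression.

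*Small cohort, HR 1.25 per SD, 150 deaths* (43% of 350). 150 × (ln 1.25)² = 7.47.

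- Continuous, linear: Φ(√7.47 − 1.96) = 78%
- Median split: Φ(√(7.47 × 0.637) − 1.96) = 59%
- 80/20 split: Φ(√(7.47 × 0.490) − 1.96) = 48%
- Ordered groups scored as a 1-df trend: tertiles 68%, quartiles 72%, quintiles 74%

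At 200 deaths the first three become 88%, 71% and 60%.

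*Large cohort, HR 1.2 per SD, 1,000 events.* Continuous 100%, quartile trend 100%, median split 99.6%, 80/20 split 98%. A weaker effect still suffers at this event count: at HR 1.1 the continuous, median and 80/20 figures are 85%, 67% and 56%. At 5,000 events and HR 1.1 all are at least 99.7%.

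**The price of a spline.** If the effect is in fact linear, a joint test has the same non-centrality (7.47) spread over more degrees of freedom. From the non-central chi-square at the 5% level, power is about 69% with 2 df and 62% with 3 df, against 78% for the linear term. Unordered categories pay a similar price: tertiles tested jointly on 2 df have non-centrality 7.47 × 0.793 = 5.92 and power of about 58%.

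**Where it falls.** The cohorts of 350 to 500 are kidney, uterine body, uterine cervix, gastrointestinal stromal tumour and liver: 3 × 350 + 2 × 500 = 2,050 patients. The cohorts of 5,000 to 10,000 hold 3 × 10,000 + 2 × 5,000 = 40,000, or 82% of 48,850.

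**The case against.** The strongest objection is about scope. The categorical wording sits in the sentence on univariate logistic regression and governs nothing else. A reader might infer that all prognostic factors are to be entered as categories throughout, that factors finally called important therefore depend on the cut-points, and that residual confounding follows. The article does not support this. It does not state the coding in the Cox and parametric models, where importance is judged, and it does not say that univariate results decide which variables enter them. Univariate models adjust for nothing, so residual confounding does not arise at this step. This objection stands, and the point is confined to the univariate regressions.

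The second objection is about size. A reader might take a loss of a third to a half as a property of the plan. That range needs exactly two groups, cut between the median and about 80/20, and the article states no number of groups. With three to five groups the loss is 21% to 10%. This also stands, so both ranges are given.

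Third, most patients are in cohorts large enough to absorb the loss, and a spline gives back part of the gain. Both are true. In the large cohorts the dependence on cut-points remains even where power does not suffer.

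Fourth, if an effect is a true threshold, categories can fit better than a single straight line. That argues for allowing a flexible term where non-linearity is plausible. It does not argue for categorising every factor.

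Finally, Table 2 lists what is collected, not the factors finally chosen. It is therefore fair to say that many candidate factors are continuous, but not that most of the analysed ones are.

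**Conclusion.** The point holds for the univariate logistic regressions. Section 2.5 fixes a coding that is inferior for continuous factors, and gives no cut-points.

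For a roughly normal factor with a linear effect, the loss is about 36% to 51% of the information if two groups are used, and about 21% to 10% with three to five. At an assumed HR of 1.25 per SD and 150 deaths, a two-group split takes power from 78% to between 59% and 48%. The power loss matters mainly in the five cohorts of 350 to 500 patients. It is small in those of 5,000 to 10,000 unless the effect is weak and events are few. These figures rest on assumed event counts, effect sizes and splits, because the article gives none.

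No conclusion is drawn about the Cox or parametric models beyond the observation that their coding is not stated.

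**What to change.** In section 2.5, replace the instruction to use categorical values with wording to this effect:

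- In the univariate regressions, continuous factors enter as continuous: log-transformed where skewed (tumour markers, enzymes), as a linear term by default, and as a low-df restricted cubic spline where non-linearity is plausible. Naturally categorical or ordinal factors stay as they are.
- The same coding carries into the Cox and parametric models.
- Fixed categories, stated in advance, are used for Kaplan–Meier curves and for displaying results.

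The study is retrospective and data collection is unaffected, so the change is to the analysis text only. The cost is 1 to 2 extra degrees of freedom per spline and a plot in place of a single ratio. In the small cohorts a spline is not free: under the assumptions above, a joint test on 2 or 3 df has about 69% or 62% power against 78% for a linear term. That is the reason to make the linear term the default and to reserve splines for factors where the shape is in real doubt.
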